#### Secondary outcomes

2.8.2

The secondary endpoint is the change in TSH from baseline to week 12. Biochemical measurements of TSH levels will be performed in the laboratory of each center at 4 weeks’ interval. In addition, the change in blood lipids, including the total cholesterol, triglyceride, high-density lipoprotein will be measured.

#### Safety assessments

2.8.3

Safety will be assessed in terms of the vital signs, and routine renal function, liver function, blood, urine, stool, and electrocardiogram test results obtained during the screening period and after 12 weeks of treatment. Adverse events, vital signs, and laboratory examinations will be recorded on a case report form before and after patients take their medication at every visit. Adverse events are defined as any unexpected sign or symptom during the trial period, and participants will be asked to inform clinicians about the occurrence of any adverse events while taking their medication. All information about adverse events will be recorded in detail, such as the duration and extent of the adverse event, relationship with the trial medicine, and name of the suspected drug. Common adverse events may include gastrointestinal side effects, such as stomach discomfort, nausea, and diarrhea, which are not expected to be severe. However, if serious adverse events occur that may lead to death or require extended hospitalization, the participants will be asked to quit the clinical trial as soon as possible, and proper treatment will be provided.

### Statistics

2.9

#### Sample size

2.9.1

This study is a trial of a new therapeutic regimen of SD treatment. In a similar study conducted previously on selenium supplementation, the total sample size was 192 participants.^[35]^ Allowing for a 20% withdrawal rate, we plan to include 228 patients in this trial.

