**Methods and analysis::**

This study is a randomized, double-blind, and controlled clinical trial. A total of 228 participants with the diagnosis of mild SCH will be randomly assigned to the SD or placebo group in a ratio of 1:1. Participants will receive treatment for 12 weeks and undergo 12-month follow-up. The primary outcome measure is the thyroid-stimulating hormone level, and secondary outcomes will be the differences in the results of Thyroid-related Quality of Life Questionnaire, blood lipids, and Traditional Chinese Medicine Symptom Score Scale between baseline and at 12 weeks after intervention.

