SD, a formula comprised of multiple herbs, such as, *Pinellia ternata (Thunb.) Breit.*, *Magnolia officinalis Rehd. et Wils* and *Prunella vulgaris L*., and so on is a frequently prescribed TCM in patients with mild SCH. Based on TCM theory, it can improve the symptoms of depression, fatigue, and hypothyroidism. SD evolved on the basis of the Banxia-houpu decoction. *Jin Gui Yao Lue* by the reputed TCM doctor Zhang Zhongjing of the Han Dynasty stated that a Banxia-houpu decoction could be used to improve depression and throat discomfort. An in vivo study reported that Banxia-houpu decoction can increase the anti-stress effect through the hypothalamus-pituitary-adrenal gland axis and modification of stress behaviors.^[25]^ Water extract of *Magnolia officinalis Rehd. et Wils* has antidepressant-like effects by improving the hypothalamus-pituitary-adrenal axis function, promoting expression of brain-derived neurotrophic factor in the hippocampus, and increasing hippocampal neurogenesis.^[26]^ Autoimmune thyroiditis is the most common endogenous cause of SCH.^[27]^ The active ingredients of *Magnolia officinalis Rehd. et Wils* can strengthen innate immune signaling responses and modulate inflammation^[28,29]^; whereas, the active ingredients of *Poria cocos (Schw.) Wolf* can regulate mammalian immune cells, with potential for use in treating Th2-mediated immune disorders.^[30]^

In a preliminary study including a small sample, SD showed effect to improve symptoms in patients with mild SCH and reduce TSH levels; however, there have been a few high-quality trials and more evidence is needed to prove the therapeutic effect of SD. This study aims to evaluate the effectiveness and safety of SD in patients with mild SCH using strict high-quality methodology per Consolidated Standards of Reporting Trails (CONSORT) statement for randomized controlled trials of herbal medicine.^[31]^

The results of this trial will hopefully provide clinical evidence for the treatment of patients with mild SCH.

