### Randomization, allocation concealment, and blinding

2.5

Participants will be randomly assigned to either the SD or placebo group in a 1:1 ratio. Randomization using Statistics Analysis System (SAS) software will be performed by independent staff statisticians. The randomization numbers are kept in opaque sealed envelopes.

Allocation concealment will be performed by the Data Management Center of Guang’anmen Hospital. Randomization code generation and drug blinding will be implemented independent of the data collection, evaluation, and analysis. The drug administrator at each participating medical center will enroll patients sequentially on the basis of screening order. Both participants and investigators will be blinded to the allocation until completion of the trial. To achieve blinding, the same kind of packaging will be used for both the drug and placebo in each group. The placebo will be matched to the corresponding medicine in terms of size, color, shape, taste, and smell by adding artificial pigment.

Twenty-four-hour emergency code break and medical information will be provided by the Data Management Center of Guang’anmen Hospital. Each subject will be allowed access to the investigator through telephone in case of emergency. In case of a severe adverse event, an administrator will unblind the patient information as an emergency and provide relevant treatment.

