#### Primary outcomes

2.8.1

The primary endpoint is the change in Thyroid-related Quality of Life Questionnaire (ThyPRO) results from baseline to week 12, with severity rating on a scale of 0 to 100 at 0, 4, 8, and 12 weeks from the start of the treatment period.^[10,34]^

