#### Data analyses

2.9.2

Statistical Package for the Social Sciences (SPSS) version 17.0 (SPSS, Inc., Chicago, IL) software will be used for data analysis. An intention-to-treat analysis will be conducted for patients who underwent treatment at least once. Continuous data with normal distribution will be presented as mean ± standard deviation, and those without normal distribution as median (interquartile range). Statistical comparisons will be analyzed using the student *t* test, and Wilcoxon rank sum test for continuous data and *χ*^*2*^ test for categorical data. Differences between groups will be evaluated using the *χ*^*2*^ test or Wilcoxon rank sum test. All statistical tests will be 2-sided tests, and *P*-value of < .05 will be considered statistically significant.

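### The sample-size figures do not fit together: 228 less 20% withdrawal leaves about 182, not 192, and the 192 is another trial's total, tied to no effect on this trial's endpoint

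*Protocol article*

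**What the plan says.** Section 2.9.1 (Sample size) of the protocol article gives one basis for the trial's size: "In a similar study conducted previously on selenium supplementation, the total sample size was 192 participants". It then adds: "Allowing for a 20% withdrawal rate, we plan to include 228 patients in this trial". It states no target difference, standard deviation (SD) or power.

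Other parts of the article bear on the number:

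- **Allocation (section 2.5):** "Participants will be randomly assigned to either the SD or placebo group in a 1:1 ratio", so 228 means 114 per arm.
- **Significance level (section 2.9.2):** "All statistical tests will be 2-sided tests, and *P*-value of < .05 will be considered statistically significant". This is stated for the analysis and is not linked to the sample size.
- **Primary endpoint:** section 2.8.1 says "The primary endpoint is the change in Thyroid-related Quality of Life Questionnaire (ThyPRO) results from baseline to week 12", while the abstract says "The primary outcome measure is the thyroid-stimulating hormone level".
- **Earlier data on the study drug (Introduction):** "In a preliminary study including a small sample, SD showed effect to improve symptoms in patients with mild SCH and reduce TSH levels".

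**The concern.** There are two faults in one short paragraph.

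First, the three printed numbers (192, 20% and 228) should be linked by a simple inflation for withdrawal, and they are not. A reader who takes the paragraph at face value will believe that 192 patients remain after 20% withdrawal. About 182 would.

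Second, the starting figure is the headcount of a trial of a different intervention. Nothing in the paragraph connects 192 to a difference in ThyPRO or TSH that this trial should be able to detect. The article therefore gives a number of patients but no statement of what that number can show. The Introduction mentions a small preliminary study of the decoction itself, which would have been a more relevant starting point if it holds usable variability data.

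**Working it through.** **Inputs.** Base 192, withdrawal 20% and enrolment 228 (section 2.9.1); 1:1 allocation (section 2.5); two-sided 5% (section 2.9.2). Power is not stated, so 80% and 90% are used below as assumptions. The SD is not stated either, so differences are given in SD units.

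**1. Trying to reproduce 228.**

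- Correct inflation, n/(1 - w): 192/0.80 = 240 (120 per arm). The stated 228 is 12 short.
- Common mistaken inflation, n x (1 + w): 192 x 1.20 = 230.4, rounded up to 231. This is close to 228 but not equal to it.
- Working backwards: 228/1.20 = 190 exactly, but 190 appears nowhere in the article. 228/192 = 1.1875, a mark-up of 18.75%.

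Neither form of inflation gives 228 from 192 and 20%.

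**2. What 228 delivers.**

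- Retained at 20% withdrawal: 228 x 0.80 = 182.4, about 182 in total or 91 per arm.
- Shortfall against 192: 192 - 182.4 = 9.6, about 10 patients (5%).
- Largest withdrawal rate that still leaves 192: 1 - 192/228 = 15.8%.

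**3. Cost in power, under assumed targets.** In the normal approximation for two means, power = Φ(d x √(n/2) - 1.960), with n per arm and d the standardised difference. Fix d so that 96 per arm has the assumed power, then move to 91.2 per arm. The term d x √(n/2) shrinks by √(91.2/96) = 0.9747.

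- If 192 gave 80%: 2.802 x 0.9747 - 1.960 = 0.771, power 78.0%.
- If 192 gave 90%: 3.242 x 0.9747 - 1.960 = 1.199, power 88.5%.

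A t-test calculation at 91 per arm gives 77.8% and 88.4%. The loss is about 2 power points in either case.

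**4. Detectable standardised difference.** d = (1.960 + z) x √(2/n), with z = 0.842 for 80% power and 1.282 for 90%.

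| Per arm | Meaning | 80% power | 90% power |
|---|---|---|---|
| 91 | 228 less 20% | 0.42 | 0.48 |
| 96 | 192 retained | 0.40 | 0.47 |
| 114 | all 228 contribute | 0.37 | 0.43 |

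The 192 itself cannot be reproduced, because no effect, SD or power is printed from which to derive it.

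**The case against.** **192 as the required number is inferred.** The section reports 192 only as the earlier trial's total. It does not say that this trial needs 192 patients with week-12 data, nor whether 192 were enrolled or completed in the earlier trial. If they were enrolled, 192 may already include that trial's own losses. This stands as a caveat. It does not make the figures agree: the sentence order makes 192 the base for the allowance, and neither form of inflation turns 192 and 20% into 228.

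**The analysis is by intention to treat.** Section 2.9.2 keeps every patient treated at least once, and visits at weeks 4 and 8 may supply data on those who leave early. So 182 is the number expected to complete, not necessarily the number analysed. This stands in part, and is why the 114-per-arm row is shown. It does not rescue the paragraph, which itself treats withdrawals as lost information by adding an allowance for them.

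**A journal article condenses the full protocol.** Effect size, SD and power may well be set out there, and their absence alone would be no finding. But the article prints a rationale, and that rationale is inconsistent in its arithmetic and rests on an unsuitable base.

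**The effect is small.** This is correct for the arithmetic part. A reader might infer that the trial is seriously underpowered, or that a null result could not be interpreted. The documents support neither. No target effect is stated against which to call the trial underpowered, and a confidence interval for the treatment difference will show which effects are excluded, whatever the planning rationale was. The Discussion already names the small sample as a limitation.

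**Conclusion.** The point holds in a limited form. The printed figures are inconsistent: with 192 read as the number to retain, 20% withdrawal requires 240, while 228 leaves about 182 and protects 192 only up to 15.8% withdrawal. The shortfall is about 10 completers, worth roughly 2 power points if 192 had been sized for 80% power (a little less at 90%); both power levels are assumptions.

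The heavier fault is that the only printed basis for 192 is a selenium trial's total, which is tied to no effect on this trial's endpoint. That cannot be put right until the abstract (TSH) and section 2.8.1 (ThyPRO) name the same primary endpoint. Nothing here shows that more patients must be recruited. It shows that the stated justification is wrong as written and needs correcting.

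**What to change.** Text changes only, in this order:

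1. Settle whether TSH or ThyPRO is the primary endpoint, and make the abstract and section 2.8.1 agree.
2. In section 2.9.1 keep 228 and restate what it yields, for example: *228 randomised; about 182 (91 per arm) with week-12 data at 20% withdrawal; 192 only if withdrawal is at most 15.8%.*
3. Replace the selenium rationale with the detectable standardised difference at two-sided 5%: 0.42 SD for 80% power and 0.48 SD for 90% power at 91 per arm, or about 0.37 SD for 80% power if all 114 per arm contribute under the intention-to-treat set of section 2.9.2. State which of the two counts applies to the primary analysis.
4. Convert that difference to mU/L or ThyPRO points if a usable SD exists. The preliminary study is one possible source, but the article does not say that it measured ThyPRO or that it provides an SD, so this step is conditional.

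The cost is a slightly less favourable stated number of patients with week-12 data. No extra patients or procedures are needed. Stating a detectable difference discloses what 228 can show. It does not by itself establish that an effect of that size is plausible or clinically important, and the authors should comment on that.

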#### Data analyses

2.9.2

Statistical Package for the Social Sciences (SPSS) version 17.0 (SPSS, Inc., Chicago, IL) software will be used for data analysis. An intention-to-treat analysis will be conducted for patients who underwent treatment at least once. Continuous data with normal distribution will be presented as mean ± standard deviation, and those without normal distribution as median (interquartile range). Statistical comparisons will be analyzed using the student *t* test, and Wilcoxon rank sum test for continuous data and *χ*^*2*^ test for categorical data. Differences between groups will be evaluated using the *χ*^*2*^ test or Wilcoxon rank sum test. All statistical tests will be 2-sided tests, and *P*-value of < .05 will be considered statistically significant.

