### Follow-up

2.7

All included participants will be re-evaluated at 6, and 12 months through phone calls or as outpatients. Participants with worsened thyroid function will receive a supply of relevant medicine and a written withdrawal schedule.

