#### Participant retention and withdrawal

2.9.4

Participants may withdraw from the trial at any time for any reason, and the reason will be recorded in the CRFs. The investigator will inform the participants that they have the right to withdraw from the research project and will be provided with standardized treatment to ensure their safety under the following conditions: rapidly decreasing estimated glomerular filtration rate to below 30 mL/min/1.73 m^2^, alanine transaminase or aspartate aminotransferase level 2-fold higher than the normal limits, or serum creatinine level beyond the normal range; serious complications or deterioration of existing health condition; poor participant compliance, such as actual drug use of less than 80% or more than 120% of the prescribed dose; or use of proscribed drugs during the study. Participants in this trial will be provided with cost-free drugs and scheduled examinations. Necessary examinations and treatments will also be provided for any adverse event.

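### Events after randomisation are tied to leaving the study, not only to stopping product, so the week-12 data needed for the announced intention-to-treat analysis are not secured

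*Protocol article*

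**What the plan says.** Four places in the protocol article bear on this.

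- **Section 2.9.2, Data analyses.** "An intention-to-treat analysis will be conducted for patients who underwent treatment at least once". No participant is excluded for compliance, completion or use of other drugs.
- **Section 2.8.3, Safety assessments.** If a serious adverse event occurs that may lead to death or prolonged hospital stay, "the participants will be asked to quit the clinical trial as soon as possible, and proper treatment will be provided".
- **Section 2.9.4, Participant retention and withdrawal.** "The investigator will inform the participants that they have the right to withdraw from the research project" under listed conditions. These cover changes in kidney or liver tests, serious complications or worsening health, "poor participant compliance, such as actual drug use of less than 80% or more than 120% of the prescribed dose", and "use of proscribed drugs during the study".
- **Section 2.7, Follow-up.** "All included participants will be re-evaluated at 6, and 12 months through phone calls or as outpatients".

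The endpoints in sections 2.8.1 and 2.8.2 are changes in ThyPRO and TSH from baseline to week 12. Section 2.6 sets visits at weeks 0, 4, 8 and 12. Section 2.9.1 allows for 20% withdrawal in a total of 228.

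**The concern.** An intention-to-treat comparison needs outcomes from participants whatever happens to them after randomisation. The listed events all happen after randomisation, and several can depend on treatment or outcome: poor tolerance, low adherence, deterioration. If they end participation and not just dosing, the week-12 value is missing for a group that need not resemble those who stay. A missing-data method can model such gaps under assumptions, but no analysis plan can recover measurements that were never taken.

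Safety is affected too. Section 2.8.3 schedules laboratory tests and the electrocardiogram at screening and after 12 weeks. Participants with the most serious events are the ones asked to leave before the second of these.

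A smaller point is the label. A set that requires at least one treatment is a modified intention-to-treat set.

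**Working it through.** **Step 1. What is secured after exit.**

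| Event | Wording of the exit | Week-12 assessment after exit stated? |
|---|---|---|
| Serious adverse event (2.8.3) | asked to quit the clinical trial | no |
| Laboratory change or deterioration (2.9.4) | right to withdraw from the research project | no |
| Drug use below 80% or above 120% (2.9.4) | the same | no |
| Proscribed drugs (2.9.4) | the same | no |

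The article never describes stopping product while remaining in the study. The 6- and 12-month re-evaluation in section 2.7 covers all included participants, but it comes after week 12 and may be by phone, which cannot supply a TSH measurement. It does not replace the week-12 value.

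**Step 2. Scale of planned loss (section 2.9.1).** The plan starts from 192, allows 20% withdrawal and arrives at 228. Multiplying gives 192 × 1.2 = 230.4, close to 228 but not equal to it; dividing gives 192 / 0.8 = 240. The figure serves here only for scale: 0.20 × 228 = 45.6, about 46 participants, leaving 182.4, about 91 per arm. The 20% covers withdrawal for any reason, so it is an upper guide to what these rules could cause.

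**Step 3. Size of a possible bias.** The document gives no exit rates by arm and no leaver profiles, so these are assumptions:

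- no true treatment effect and outcome SD of 1;
- 114 per arm (228 / 2, from the 1:1 allocation);
- only stayers have a week-12 value;
- leavers differ from stayers by m SD, the same in both arms.

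With proportion d leaving an arm whose overall mean is 0, the stayer mean s satisfies (1 − d)s + d(s + m) = 0, so s = −d·m. The bias in the difference between arms has size |d₁ − d₂| × m. Its standard error is √(1/n₁ + 1/n₂), with n = 114(1 − d). For 25%/15% this is √(1/85.5 + 1/96.9) = 0.148. For 30%/10% it is √(1/79.8 + 1/102.6) = 0.149. The type I error is that of a two-sided 5% test shifted by the bias divided by its standard error.

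| Withdrawal by arm | m = 0.25 | m = 0.5 | m = 1.0 |
|---|---|---|---|
| 20% / 20% | 0 SD; 5.0% | 0 SD; 5.0% | 0 SD; 5.0% |
| 25% / 15% | 0.025 SD; 5.3% | 0.05 SD; 6.3% | 0.10 SD; 10.3% |
| 30% / 10% | 0.05 SD; 6.3% | 0.10 SD; 10.3% | 0.20 SD; 26.8% |

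**Step 4. Equal rates, different reasons.** If leaver profiles differ, the bias is |d₁m₁ − d₂m₂|. With 20% leaving each arm, leavers 0.5 SD worse in one arm and random in the other, it is 0.20 × 0.5 − 0.20 × 0 = 0.10 SD. Equal rates alone therefore do not remove the risk; the kind of leaver must match as well.

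**The case against.** The strongest reply is that the article does not say what a hurried reader might infer: that non-compliant participants must be removed and the primary analysis is confined to compliant completers. Section 2.9.4 speaks of a right to withdraw, section 2.9.2 keeps everyone treated at least once, and the 80-120% limits are nowhere tied to an analysis set. Section 2.7 re-evaluates all included participants without excepting those who left, and section 2.9.4 promises necessary examinations after any adverse event. This is also a condensed article, and missing-data handling or a per-protocol set may well stand in the analysis plan.

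Most of this stands. Removal for poor compliance or proscribed drugs is not clearly compulsory, no set of compliant survivors is defined, and silence on week-12 assessment after exit is not a statement that none is made. No fault is found here with missing-data methods left to another document. The one-dose requirement is also minor: under double-blinding with a matched placebo, failing to take a first dose can hardly depend on allocation.

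What remains is narrower. Section 2.8.3 does direct participants out of the trial. In section 2.9.4 a right to withdraw at any time for any reason is already granted, so a further list naming compliance and proscribed drugs is naturally read as exit criteria, and three centres could apply it differently. Whether visits continue once product stops is a matter of trial conduct that these two sections settle badly as worded.

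**Conclusion.** The concern holds as a risk, not as a demonstrated bias. Sections 2.8.3 and 2.9.4 tie events after randomisation to leaving the study and do not separate this from stopping product, so week-12 ThyPRO, TSH and safety data are not secured for the participants concerned. The analysis in section 2.9.2 depends on those data, whichever of ThyPRO or TSH is taken as primary.

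Bias needs two conditions together: exit related to outcome, and a difference between arms in the rate or the kind of exit. On the assumed leaver differences, the range is none under equal and similar exit and 0.025 to 0.10 SD at 25%/15%, with a type I error of 5.3% to 10.3%. The document gives nothing by which to choose among these cases.

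A reader might go further and suppose that one arm loses exactly its worst 20% while the other loses 20% at random, which would give φ(−0.842) / 0.8 = 0.35 SD. Nothing in the document supports that pattern. Nor can the bias be set against a planned effect, because no power, SD or effect size is stated. The case for change rests on its low cost and on the fact that lost week-12 data cannot be restored later.

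**What to change.** 1. Leave the conditions for stopping product as they are. Reword sections 2.8.3 and 2.9.4 so that those conditions concern study product only, and keep the participant's right to withdraw consent as a separate matter.
2. State that all randomised participants continue the scheduled week 4, 8 and 12 assessments (ThyPRO, TSH, adverse events and the planned week-12 safety tests) unless they withdraw consent.
3. In section 2.9.2, define the primary analysis set as all randomised participants in their assigned arm, including data collected after product is stopped. If the one-dose condition is kept, call the set modified intention-to-treat.
4. Use 80-120% compliance only to define a per-protocol sensitivity set.

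The cost is changed protocol and consent wording, plus attendance by a minority at visits that are already scheduled. The downside is that the estimate will include off-product data and may be slightly smaller. The change helps only participants who have not yet left, so it should be made early.

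### Two sentences in Data analyses disagree on the between-group test for continuous outcomes, and no named test adjusts week-12 change for the baseline value already collected

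*Protocol article*

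**What the plan says.** Section 2.9.2 (Data analyses) has two consecutive sentences on tests. The first lists the Student t test "and Wilcoxon rank sum test for continuous data", and the chi-square test for categorical data. The second begins "Differences between groups will be evaluated using the" and names the chi-square test or the Wilcoxon rank sum test; the t test does not appear.

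Normality enters the section once, for description: "Continuous data with normal distribution will be presented as mean" with standard deviation, and otherwise as median with interquartile range. On error rates it says "All statistical tests will be 2-sided tests", with significance at a P "value of < .05 will be considered statistically significant".

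Section 2.8.1 defines the endpoint: "The primary endpoint is the change in Thyroid-related Quality of Life Questionnaire (ThyPRO) results from baseline to week 12". The same section has the questionnaire scored at four visits, "with severity rating on a scale of 0 to 100 at 0, 4, 8, and 12 weeks". Section 2.8.2 makes change in TSH to week 12 a secondary endpoint, and says that "TSH levels will be performed in the laboratory of each center". There are three centres. The analysis section names no covariate.

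**The concern.** The main comparison is between two groups on a continuous change score. The first sentence allows two tests for it. Under the second, only the Wilcoxon test is applicable, since chi-square does not suit a continuous score. The two tests answer different questions. The t test concerns the difference in mean change. The Wilcoxon test concerns whether values in one group tend to exceed those in the other, and gives no mean difference on the ThyPRO or TSH scale. If they fall on opposite sides of 0.05, the article does not say which one decides.

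The second issue is precision. A plain comparison of change subtracts the whole baseline value, although the regression of week 12 on baseline usually has a slope below one. Using baseline as a covariate lets the data set that slope. The Discussion calls the sample small, and section 2.9.1 gives no power, effect size or SD, so avoidable loss of precision matters.

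**Working it through.** **The plan's own figures.** There is no power, SD or effect size to reproduce. The only usable inputs are 228 participants and a 20% withdrawal allowance (section 2.9.1): 228 × 0.8 = 182.4, about 91 per arm.

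**Which test applies to week-12 change?**

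| Sentence in 2.9.2 | t test | Wilcoxon | Chi-square |
|---|---|---|---|
| First (by data type) | yes, continuous | yes, continuous | categorical |
| Second (group differences) | not named | yes | yes |

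The sentences agree on Wilcoxon and disagree on the t test. Neither gives a rule for choosing.

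**What the open choice could cost.** Type I error at nominal 0.05 was simulated with 10,000 runs and 91 per arm:

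| Data | t test | Wilcoxon | Shapiro pre-test, then t or Wilcoxon | Smaller of the two P-values |
|---|---|---|---|---|
| Normal | 0.048 | 0.048 | 0.048 | 0.057 |
| t, 5 df | 0.050 | 0.051 | 0.052 | 0.066 |
| Lognormal | 0.050 | 0.049 | 0.049 | 0.071 |

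Either test alone is close to nominal, and so is a strict pre-test rule. Error rises only if the test is picked by its result.

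**Efficiency.** Let s be the SD at both times and rho the baseline-to-week-12 correlation. Rho is not in the documents and is assumed to be 0.3 to 0.8.

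- Variance of change: 2s²(1 − rho)
- Variance after adjustment for baseline: s²(1 − rho²)
- Ratio: (1 + rho)/2

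Take an effect with 80% power on unadjusted change at two-sided 0.05. Then 1.960 + 0.842 = 2.802, and adjusted power = Φ(2.802/√ratio − 1.960). The n per arm for 80% power is 91 × ratio, rounded up.

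| rho | Ratio | Adjusted power | n per arm for 80% |
|---|---|---|---|
| 0.3 | 0.65 | 93.5% | 60 |
| 0.5 | 0.75 | 89.9% | 69 |
| 0.7 | 0.85 | 86.0% | 78 |
| 0.8 | 0.90 | 84.0% | 82 |

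**Unequal variances.** Let k = baseline SD / week-12 SD. The ratio is (1 − rho²)/(1 + k² − 2·rho·k). The denominator minus the numerator is (k − rho)², so adjustment does not increase the variance in this calculation, and it gains nothing when k = rho.

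- rho = 0.5, k = 1: 0.75/1.00 = 0.75
- rho = 0.5, k = 0.75: 0.75/0.8125 = 0.92
- rho = 0.5, k = 0.5: 0.75/0.75 = 1.00

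This bears on TSH. Entry requires 4.6 to 10.0 mU/L (section 2.4.2), which limits the spread at baseline but not at week 12, so k is likely to be below 1.

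**The case against.** The strongest objection is that a journal article condenses the full protocol, and the model specification may be in an analysis plan that is not shown. This stands for anything the article leaves out. It does not cover the test sentences, because the article does state its tests and states them inconsistently. The second sentence could also be meant for categorical or non-normal data only. It does not say so, and it does not contain the word only; the conflict is that it names tests for group differences and omits one just assigned to continuous data.

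The precision figures use no trial data. The 80% power, rho and equal variances are all assumed, and with a narrow baseline spread the gain can disappear. That stands, and the range above shows it.

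Several stronger readings are tempting but unsupported:

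- A reader might infer that a normality check selects the test. The article ties normality to presentation only, and a strict rule would keep type I error near nominal. Nothing plans to take the smaller P-value.
- A reader might infer that baseline is ignored. A change score subtracts it; what is absent is covariate adjustment.
- A reader might infer that participants without week 12 are dropped, so that data must be missing completely at random. No complete-case rule is stated, and handling of missing data may be in the unseen plan.
- A reader might infer that all of the roughly 46 allowed withdrawals (228 − 182) leave week 4 and 8 data unused. The timing of withdrawal is not given, and a week-12 test need not use those visits.
- A reader might infer that local laboratories bias the comparison. ThyPRO involves no laboratory. For TSH, an additive laboratory offset cancels in change if each participant stays with one laboratory, and the size of any remaining centre effect cannot be calculated.

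**Conclusion.** The point holds in two parts. First, section 2.9.2 contradicts itself on whether the t test is used for group differences, so no single test is fixed for the week-12 change endpoint. This follows from the text and needs no assumption.

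Second, the named tests leave change unadjusted for baseline. This is a loss of efficiency and does not make the comparison invalid. With equal variances and rho of 0.3 to 0.8, the avoidable part is 35% to 10% of the change-score variance, or about 13.5 to 4 power points from a hypothetical 80%. It is smaller as the SD ratio falls from 1 towards rho, and zero when the two are equal. The gain for ThyPRO may therefore exceed that for TSH, but the documents cannot settle either. The plan should be corrected before unblinding.

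**What to change.** Replace the two conflicting sentences with one prespecified primary analysis: an ANCOVA of the week-12 value with treatment, baseline value and centre. Report the adjusted difference with its 95% CI and test it at two-sided 0.05. The treatment estimate is the same whether week 12 or change is the outcome once baseline is in the model, so the endpoint definition need not change. Analyse TSH on the log scale at both times, so that a proportional difference between laboratories becomes an offset that the centre term absorbs. Keep Wilcoxon on change as a sensitivity analysis, and say that it does not replace the primary result.

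A repeated-measures model using weeks 4 and 8 is an acceptable alternative, not a requirement.

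The cost is analysis wording. Baseline values, week-12 values and centre are already collected, and no visit, measurement or participant is added.
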